# Chlorhexidine locking device for central line infection prevention in ICU patients: protocol for an open-label pilot and feasibility randomized controlled trial

**DOI:** 10.1186/s40814-020-0564-9

**Published:** 2020-02-18

**Keywords:** Sepsis, CLABSI, Central line infection, Central venous catheter, Device, Prevention, Chlorhexidine, CHG

## Abstract

**Background:**

Critically ill patients in the intensive care unit (ICU) are at risk for central line-associated bloodstream infection (CLABSI) with an incidence up to 6.9 per 1000 catheter days. CLABSI has a significant attributable mortality and increases in-hospital length of stay, readmissions, and costs. Chlorhexidine gluconate (CHG), a broad-spectrum biocide, has been shown to effectively reduce infections including CLABSI; however, few trials have utilized CHG for prevention of central line infections. Our preclinical work has demonstrated a device that diffuses CHG into the intravenous lock solution of central venous catheters and decreases bacterial growth on the catheter lumen. We designed a clinical trial to test the feasibility of using a CHG device in an ICU patient population.

**Methods:**

The proposed pilot trial will be a single centre, open-label, two-arm, parallel group feasibility randomized controlled trial (RCT). Participants will have a central line in situ and will be enrolled within 72 h of admittance to 3 ICUs at a single academic hospital. Exclusion criteria will include suspected infection, chronic indwelling catheters, and CHG allergy. Informed consent will be obtained from eligible participants or their substitute decision maker prior to randomization. Participants will be randomized to receive either usual care or the CHG locking device. Blood cultures will be drawn from all participants every 48 h. The primary objective of this study will be to determine the feasibility of using this protocol to conduct a larger trial. Feasibility will be assessed through the following outcomes: (1) consent rate, (2) recruitment rate, (3) protocol adherence, and (4) comfort level with the device. The secondary objective of this study will be to establish the preliminary efficacy of the device.

**Discussion:**

This study will be the first human RCT to investigate a CHG locking device for the prevention of central line infections. Findings from this trial will inform the feasibility of conducting a large RCT and provide preliminary data on the efficacy of a CHG locking device.

**Trial registration:**

ClinicalTrials.gov, NCT03309137, registered on October 13, 2017.

## Background

### Rationale

Vascular access via central venous catheters (CVCs) is essential for acute patient care in the Intensive Care Unit (ICU) [1]. Despite the utility of CVCs, they have been identified as a risk factor for bloodstream infection that, when not recognized early, can progress to sepsis [2, 3]. CVCs are the most common cause of nosocomial bloodstream infection [4]. A report by the National Nosocomial Infections Surveillance System identified that 87% of all primary bloodstream infections occur in patients with a CVC [5]. Additionally, the relative risk for bloodstream infection is 64 times greater for patients with a CVC compared to patients with only peripheral venous catheters [4]. Instances of bloodstream infection in patients with a CVC are formally referred to as central line-associated bloodstream infection (CLABSI) [1, 6]. Critically ill patients are among those most likely to develop CLABSI [7, 8] with incidence as high as 6.9 per 1000 catheter days [9–12]. Evidence suggests that CLABSI impacts patient mortality and increases in-hospital length-of-stay (LOS) readmissions and costs. A systematic review of 18 studies by Ziegler and colleagues found that CLABSI has a substantial attributable mortality, with an odds ratio of 2.75 for in-hospital death [13]. A 2013 meta-analysis of the burden of hospital-acquired infections (HAIs) in the USA found CLABSI has one of the highest attributable LOS of any HAI at 15.7 days, second only to *Methicillin-resistant Staphylococcus aureus* surgical site infection [14]. A retrospective case-controlled cohort study of 11,802 hospitalizations in the USA reported that 10.4% more CLABSI patients were readmitted to a hospital within 30 days of discharge compared to non-CLABSI patients [15]. CLABSI also presents a significant economic burden, increasing healthcare costs by an average of USD 45,814 per case [14, 16, 17].

Several sources of contamination contribute to the pathogenesis of CLABSI [4]. Pathogens gain access to the external surface of the CVC through transcutaneous migration, and to the luminal surface through contaminated infusate, colonization of the catheter hub, or hematogenous seeding [18]. As interventions to prevent external surface contamination are increasingly used, such as CVC insertion bundles [10, 19], hub colonization has become the dominant route of infection [18]. Once pathogens gain access to a CVC, the lumen acts as a nidus for colonization where bacteria and fungi attach and secrete gelatinous exopolymers, enclosing themselves in a protective matrix called a biofilm [20, 21]. Pathogens growing in a biofilm are particularly resistant to antibiotics and host defenses when compared to free-floating bacteria [20]. Frequent handling of a colonized catheter hub risks displacing the biofilm, potentially leading to bacterial invasion of the catheter inner lumen [22]. This risk may be increased in the ICU where frequent catheter access may occur without adequate hand hygiene or use of alcohol wipes during emergency situations or when staff-to-patient ratios are increased [22].

### Relevant medical literature

Various interventions have been suggested to lower incidence of CLABSI [23], including antimicrobial impregnation of catheters and antibiotic locking solutions. Although impregnated catheters have been shown to reduce CVC colonization, results vary based on setting, and widespread use has not been broadly recommended [24–26]. Antibiotic lock solutions have proven an effective means of decreasing incidence of CLABSI [27]; however, research has shown that their use quickly leads to antibiotic resistance [28]. Recent studies have demonstrated the effective role of topical chlorhexidine gluconate (CHG) for reducing CLABSI [29]. CHG is a broad-spectrum biocide with rapid onset of action, prolonged antimicrobial effects, and excellent efficacy against gram-positive organisms [30]. A prospective, randomized cross-over trial demonstrated that daily bathing with CHG soaked washcloths reduced the incidence of bloodstream infections from 6.60 to 4.78 cases per 1000 patients in the ICU [31]. CHG bathing decreased the likelihood of patients’ resident skin flora entering the bloodstream at the CVC insertion site or extraluminal surface of the catheter, however, manipulation of catheter hubs remains a more prominent source of infection [32]. The antimicrobial efficacy of CHG has also been shown in vitro and in preclinical animal trials in a previous study by our group [33]. CHG significantly reduced *Staphylococcus aureus* contamination, decreasing bacterial load by 6 log_10_ colony-forming units (CFU) in vitro, and by 3–4 log_10_ CFU/lumen in Yorkshire swine with a CVC inserted into the jugular vein [33]. This preclinical work informed the potential of a CHG locking device to decrease incidence of CLABSI and led to the current pilot trial.

### Overall research question

ChloraLock^TM^ (Fig. 1) is a device that instills CHG into the lock solution of venous catheters with the aim of sterilizing solutions passing into the catheter during routine locking procedures. In patients admitted to the ICU with a CVC in situ, does CHG locking solution administered by the ChloraLock^TM^ device reduce risk of intravenous line colonization and improve patient and hospital outcomes by preventing cases of CLABSI?

**Fig. 1 Fig1:**
[figure not shown]
The ChloraLock^TM^ device contains freeze-dried CHG (arrow) that dissolves with introduction of the locking solution

### Pilot trial research question

Is conducting a large randomized controlled trial (RCT) feasible using this device and protocol?

### Explanation of comparator

There are currently no antimicrobial locking solutions broadly recommended for prevention of CLABSI. Therefore, ChloraLock^TM^ will be compared to ‘usual care’.

## Methods

### Study design

The ChloraLock^TM^ pilot trial is a single centre, open-label, two-arm, parallel-group feasibility RCT. Randomization will be performed with a 1:1 allocation, and study participants and evaluators will not be blinded to intervention assignment due to lack of placebo ChloraLock^TM^ devices. Order of randomization will be concealed by means of random number generator and sealed envelopes (see Allocation and Blinding details below). Patients will be recruited from the ICU at the Hamilton General Hospital (HGH) within 72 h of admission if they have a CVC in situ. The primary objectives of the ChloraLock^TM^ pilot trial are to assess uptake of the trial protocol and ChloraLock^TM^ device by ICU staff and determine the feasibility of conducting a large RCT to investigate our overall research question. Secondary objectives are related to the clinical efficacy of the ChloraLock^TM^ device. ICU nurses will be responsible for using the ChloraLock^TM^ device and operationalizing the protocol; therefore, we will be collecting data on their perceptions of the trial using a voluntary survey. Feasibility and survey data will be used to inform the conduct of a larger RCT.

This protocol adheres to the Standard Protocol Items: Recommendations for International Trials (SPIRIT) guidelines and is formatted in accordance with the SPIRIT 2013 checklist (see Additional file 1) with all required items [34, 35]. The World Health Organization Trial Registration Dataset (see Additional file 2) and a schedule of enrollment, interventions, and assessments (Table 1) are included. Prior to enrolment of our first participant, the protocol was registered at ClinicalTrials.gov (NCT03309137).

**Table 1 Tab1:** SPIRIT figure detailing enrolment, interventions, and assessment

Timepoint	Study period							
	Enrolment	Allocation	Post-allocation					Close-out
	< 72 h post ICU admission (*-t*_1_)	0	t_1_	t_2_	t_3_	*t*_4_	etc.	intervention discontinued (*t*_*x*_)
Enrolment								
Eligibility screen	X							
Informed consent	X							
Allocation		X						
Interventions								
Usual care		X	X	X	X	X	X	
CHG locking device		X	X	X	X	X	X	
Assessments								
Baseline variables	X	X						
Recruitment rate	X	X						
Consent rate	X	X						
Initiation of study procedures		X						
Protocol adherence			X	X	X	X	X	
Comfort level			X	X	X	X	X	
Central line colonization			X	X	X	X	X	
Bacteremia			X	X	X	X	X	
LOS in ICU								X
LOS in hospital								X
ICU mortality at 28 days								X
Hospital mortality at 28 days								X

### Setting

The ChloraLock^TM^ pilot trial includes three ICUs at the Hamilton Health Sciences General Site, a large academic hospital and major cardiac surgical centre in Hamilton, Ontario, Canada. A single site was selected to determine the feasibility of conducting a larger RCT. In April 2018, the trial was expanded from our cardiac surgical ICU to both medical–surgical ICUs due to slow recruitment rates.

### Participants

Participants are patients admitted to one of our three participating ICUs at the HGH who meet the following eligibility criteria:

#### Inclusion criteria

Age greater than 18 yearsFirst ICU admission for this hospital stayPatient has ≥ 1 CVC in situCVC expected to remain in situ ≥ 72 hLess than or equal to 72 hours post-admittance to the ICU

#### Exclusion criteria

Expected discharge post-admittance to ICU is ≤ 36 hHopeless prognosis / limitation of care / palliative measures onlyAdmitted to the ICU with a known or suspected infection and receiving antibioticsPatients with a chronic indwelling central venous catheterPatients with a known CHG allergy

### Interventions

Patients will be randomized in a 1:1 ratio to either (1) usual care, or (2) CHG locking device.

Standard flushing and locking practices of central and peripheral venous catheters will be continued for participants allocated to ‘usual care’. All venous catheters will be flushed with a pre-specified volume of 0.9% Normal Saline (NS) solution ranging from 3 to 30 mL. As per hospital approved protocol, venous catheters will be flushed in a turbulent fashion to promote patency of the internal lumen. Catheters that are not infusing will be capped with a Luer lock adapter and considered locked. An additional movie file shows procedures for participants allocated to usual care in more detail (see Additional file 3).

**Additional file 3** Instructional video on procedures for participants allocated to usual care.

Participants allocated to ‘CHG locking device’ will receive ChloraLock^TM^ instillation addition to usual care. Venous catheters that are not infusing will be flushed with 0.9% NS solution as per hospital-approved protocol. Subsequently, ChloraLock^TM^ will be Luer locked onto a 3-mL 0.9% NS prefilled Posiflush^TM^ syringe, which will be treated as a single-use device to instill a pre-specified volume of CHG locking solution into the lumen of the venous catheter (Table 2). The catheter will then be capped with a Luer lock adapter and considered locked, thereby containing the CHG locking solution within the lumen. For participants in the CHG locking device group, each venous catheter will be labelled with the pre-specified volume of CHG locking solution required to lock the catheter. Before re-accessing the catheter for further sampling or infusions, all fluid will be aspirated to clear the lumen of CHG. An additional movie file shows procedures for participants allocated to CHG locking device in more detail (see Additional file 4).

**Table 2 Tab2:** Pre-specified flushing and locking volumes

Reference number	Full name	Common name	Flushing volume (mL)	Locking volume (mL)
MED-RX 10-1026	Minibore tubing with slide clamp, thinner lumen extension for peripheral IV	Normal saline lock extension (small bore)	3.0	0.5
MED-RX 10-114RL	Standard bore tubing with slide clamp, thicker lumen extension for peripheral IV	Normal saline lock extension (large bore)	3.0	1.0
Baxter JC 1946	Y-type extension set (1.8cc in total, 1.2cc per line)	Y-normal saline lock extension (per lumen)	3.0	1.0
ARROW SS-14703	ARROW multi-lumen central venous catheter	Triple lumen (per lumen)	10.0	0.5
ARROW SI-09880	ARROW percutaneous sheath introducer set	Cordis (side-arm lumen of introducer)	10.0	2.5
PICC lines	PICC lines	PICC line (per lumen)	20.0	0.5
ARROW CA-22122-F	ARROW temporary two-lumen hemodialysis catheter	Temporary hemodialysis catheter 12Fr (per lumen)	10.0	2.5^a^
MAHURKAR Elite 8888212216	Covidien MAHURKAR elite acute hemodialysis dual lumen catheter kit 13.5Fr	Acute dual lumen hemodialysis catheter 13.5Fr (per lumen)	10.0	2.5^a^

^a^4% sodium citrate solution

**Additional file 4** Instructional video on procedures for participants allocated to CHG locking device.

A single set of blood cultures will be drawn from the CVC of all study participants every 48 h beginning on the day of study enrolment until the patient has all CVCs removed, has a documented infection, or leaves the ICU. Blood cultures will be analyzed for infectious organisms in the core laboratory of the HGH.

The bedside nursing staff will perform the assigned interventions. Bedside nurses will document flushing and instillation of CHG on study-specific logs, which will be checked daily by the research staff. The only exception to the above procedures is flushing and locking of temporary and acute dialysis catheters will be carried out using 4% Sodium Citrate solution rather than 0.9% NS.

We will approach principal investigators (PIs) and research coordinators of all other studies conducted in the ICU to determine co-enrolment eligibility.

### Criteria for discontinuing allocated intervention

For a given trial participant, exit criteria from the study and assigned intervention will be as follow:
Consent for ongoing study participation is withdrawn by the study participant or their substitute decision maker (SDM).All venous catheters are discontinued.Participant experiences an adverse reaction to CHG locking solution.Death or discharge from ICU.

### Strategies to improve adherence to intervention protocol

Prior to study initiation regular in-services were held with > 80% attendance to educate the bedside nursing staff on the study protocol and ChloraLock^TM^ device. The vascular access team at the HGH helped develop a flushing and instillation taxonomy for all venous access catheters. Two bedside nurses were identified as ‘Nurse Champions’, their participation in study meetings and leadership qualities ensures they will be well positioned to be liaisons for staff who work weekend and night shifts. Upon study initiation, a one-page handout including detailed instructions for the study intervention will be distributed throughout the ICU. The research staff will visit the bedside of study participants daily to ensure that bedside nurses are educated on the protocol and oversee documentation of protocol adherence. Participants in the CHG locking device group will have all venous catheters labelled with a bright-green tag to indicate the volume of locking solution required. For all study participants, a bright-green sticker will be placed on the front of their medical chart and on the corner of their patient care plan Kardex to alert staff of trial enrolment and assigned intervention. A ‘flushing and locking log’ will be kept at the bedside of all study participants and will require nurses to document each time they access a venous catheter to perform flushing or locking procedures. We will document and report protocol deviations including failure to use ChloraLock^TM^ to administer CHG locking solution, aspirate CHG from a venous catheter upon re-accessing the line, and draw a blood culture from the CVC of a patient every 48 h.

## Outcomes

The primary outcomes of the ChloraLock^TM^ pilot trial relate to the feasibility of conducting a larger RCT.
*Consent rate* will be measured as the proportion of patients and SDMs approached who consent to participate in the trial; a successful consent rate will be defined as ≥ 80%. Consent rates will be reviewed on a monthly basis to improve enrolment practices.*Recruitment rate* will be measured as the proportion of patients eligible to participate who are randomized to the trial; successful accrual will be defined as ≥ 80%; we anticipate achieving enrolment of 100 patients within 50 weeks with an average of 2 patients enrolled per week. Screening logs will be reviewed on a weekly basis to determine eligibility rates.*Protocol adherence* will be measured as the proportion of instances when ChloraLock^TM^ is used during flushing and locking procedures; since this will be difficult to capture in a busy ICU setting, flushing and locking logs will be used as a surrogate to capture adherence. Successful protocol adherence will be ≥ 90% compliance with device use.*Level of comfort with the trial protocol* staff comfort with ChloraLock^TM^ and the trial protocol will be measured using repeated surveys throughout the duration of the trial. Vetted suggestions will be incorporated into the protocol.

The ChloraLock^TM^ pilot trial also includes secondary, clinical outcomes related to the antimicrobial efficacy of the device and prevention of central line infections.
*Central line colonization*: Rates of central line colonization in each study arm will be documented. We will define central line colonization as a positive central line culture with concurrent negative peripheral stab culture. We will not order peripheral stab cultures to avoid harm, but will collect data from those ordered by the treating team.*Bacteremia*: Rates of bacteremia in each study arm will be documented. We will define bacteremia as a positive peripheral stab culture and correlations will be done with central line cultures.*Clinical end points* will be documented for each study arm:
LOS in ICULOS in hospitalICU mortality at 28 daysHospital mortality at 28 days

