### Statistical analysis

Simple descriptive statistics will be used for feasibility outcomes and baseline demographics (Table 3). Continuous data will be tested for normality using histograms, Normal Q-Q plots, skewness, kurtosis, and the Shapiro–Wilk test. Normally distributed data will be summarized using mean and standard deviation, non-normal data will be summarized using median and interquartile range, and categorical variables will be summarized using number and percent proportion. The two treatment arms will be compared by simple statistics as the study may not be powered for the secondary outcomes. However, we will test group differences with either the independent-samples t-test or the Mann–Whitney U test. Somers’ delta (*d*) will be used to identify and measure the strength and direction of association that exists between two ordinal variables, particularly for the number of positive cultures. If there is a large treatment effect between groups, this may aid the sponsor in proceeding with larger RCT as required for regulatory approval within other countries. All statistical tests will be conducted using SPSS version 24 (IBM Corp, Armonk, NY).

**Table 3 Tab3:** Summary of primary and secondary outcomes for the ChloraLock^TM^ pilot trial

Pilot trial outcomes	Analysis	Pass threshold
Primary outcomes		
1. Consent rate: patients and SDMs approached who consent to randomization	Proportion	≥ 80%
2. Recruitment rate: eligible patients who are randomized	Proportion	≥ 80%
3. Protocol adherence: times ChloraLock^TM^ is used in conjunction with usual locking procedures	Proportion	≥ 90%
4. Comfort: staff comfort level with the device and trial protocol	Descriptive	NA
Secondary outcomes		
1. Central line colonization: assessed for each arm as positive central line culture and negative peripheral poke	Proportion	NA
2. Bacteremia: assessed for each arm as positive stab cultures	Proportion	NA
3. Clinical end points: LOS in ICU, LOS in hospital, ICU mortality at 28 days, hospital mortality at 28 days	Median or mean proportions	NA

Given the small sample size and the focus on feasibility outcomes, there will be no subgroup analyses or interim analyses. We will adhere to the intention to treat principle.

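### The colonization outcome drops culture pairs positive at both sites, so it can understate or, under some assumed rates, reverse a device benefit; no listed outcome is line-concordant bacteremia

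*Protocol article*

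**What the plan says.** The Outcomes section of the protocol article defines two microbiological secondary outcomes. For the first: "We will define central line colonization as a positive central line culture with concurrent negative peripheral stab culture". For the second: "We will define bacteremia as a positive peripheral stab culture and correlations will be done with central line cultures". Table 3, under Statistical analysis, repeats both rules. Colonization is "assessed for each arm as positive central line culture and negative peripheral poke" and the other entry is "Bacteremia: assessed for each arm as positive stab cultures". Both are to be summarised as proportions per arm, with no pass threshold.

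The two kinds of culture are obtained differently. Under Interventions: "A single set of blood cultures will be drawn from the CVC of all study participants every 48 h beginning on the day of study". Sampling stops when no CVC remains, an infection is documented or the patient leaves the ICU. The line culture is thus blood drawn through the catheter. For the peripheral culture, Outcomes says: "We will not order peripheral stab cultures to avoid harm, but will collect data from those ordered by the treating team".

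The article introduces these outcomes as "secondary, clinical outcomes related to the antimicrobial efficacy of the device and prevention of central line infections". The Overall research question asks whether the device will "reduce risk of intravenous line colonization and improve patient and hospital outcomes by preventing cases of CLABSI". The remaining secondary outcomes are lengths of stay and mortality.

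**The concern.** Under Rationale, the article describes organisms colonizing the catheter hub and lumen as the start of the path to bloodstream infection. A line that is culture-positive while the peripheral blood is also positive may be a more advanced state of the same process. The colonization definition excludes that pair. It passes to bacteremia, where it is counted with bloodstream infections that have nothing to do with the line.

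Two consequences follow. The colonization proportion depends on how often positive lines are also peripheral-positive, as well as on how often lines are positive. If the device changes the first quantity, the comparison between arms is distorted. Also, no listed outcome counts patients with the same organism in line and peripheral blood, although preventing CLABSI is the stated long-term aim.

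The article promises preliminary efficacy data, and Statistical analysis says that a large difference between arms could help the sponsor move to a larger trial. A figure that can shrink or change sign for definitional reasons is weak input to that decision.

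**Working it through.** **Inputs.** The definitions are those quoted above. Sample size gives 50 per arm (50 + 50 = 100, not disputed here). The article gives no expected rate of line positivity, colonization or bacteremia, so all rates below are assumptions, and peripheral results are taken as available for every positive line culture.

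**Formulas.** In each arm, with n = 50:

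- any positive line culture = n·c
- positive at both sites = n·c·s
- colonization as defined = n·c·(1−s)

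With C for control and T for device, the ratio of the defined outcome is (cT/cC) × (1−sT)/(1−sC). If sT < sC, it exceeds cT/cC, so the benefit is understated. It exceeds 1, against the device, when cT/cC > (1−sC)/(1−sT). If sT = sC, it equals cT/cC.

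**Expected counts, control v device.**

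| c | s | Any line-positive (ratio) | Both sites positive | Colonization as defined (ratio) |
|---|---|---|---|---|
| 20% v 16% | 50% v 12.5% | 10 v 8 (0.80) | 5 v 1 | 5 v 7 (1.40) |
| 20% v 20% | 50% v 0% | 10 v 10 (1.00) | 5 v 0 | 5 v 10 (2.00) |
| 20% v 14% | 50% v 1/7 | 10 v 7 (0.70) | 5 v 1 | 5 v 6 (1.20) |
| 20% v 14% | 25% v 0% | 10 v 7 (0.70) | 2.5 v 0 | 7.5 v 7 (0.93) |
| 20% v 16% | 10% v 0% | 10 v 8 (0.80) | 1 v 0 | 9 v 8 (0.89) |
| 20% v 10% | 50% v 50% | 10 v 5 (0.50) | 5 v 2.5 | 5 v 2.5 (0.50) |

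In the first three rows the defined outcome goes against the device. In the next two it understates the benefit. In the last, with equal s, the ratio is unchanged.

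**Break-even.** The relative cut in line positivity that the device must exceed for the defined outcome to favour it is 1 − (1−sC)/(1−sT):

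| sC | sT = 0 | sT = sC/2 |
|---|---|---|
| 0.1 | 10% | 5.3% |
| 0.2 | 20% | 11.1% |
| 0.3 | 30% | 17.6% |
| 0.4 | 40% | 25% |
| 0.5 | 50% | 33.3% |

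**Bacteremia.** Assume line-related bacteremia of 8% v 2% (ratio 0.25). With 4% from other sources in each arm, the listed outcome is 12% v 6% (0.50). With 10% it is 18% v 12% (0.67).

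**Does an organism match isolate line-related events?** Take the third row, with 5 v 1 positive at both sites because of the line, and add 4 other-source bacteremias per arm. The listed bacteremia outcome is 9 v 5 (0.56).

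- If none of the 4 grows from CVC-drawn blood, same-organism bacteremia is 5 v 1 (0.20) and any line-positive is 10 v 7 (0.70).
- If all 4 do, same-organism bacteremia is 5+4 = 9 v 1+4 = 5 (0.56) and any line-positive is 10+4 = 14 v 7+4 = 11 (0.79).

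In both cases colonization as defined stays 5 v 6. An organism match therefore removes between all and none of the dilution, depending on how often other-source bacteremia also grows from the catheter sample.

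**The case against.** The negative-peripheral requirement has a purpose. The line culture is blood drawn through the CVC, so organisms circulating from the lung, abdomen or a wound can grow in it even when the lumen is clean. Requiring a negative peripheral culture keeps growth confined to the line apart from circulating infection. This stands, and it is why the current definition should be kept as one component.

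The criterion is also concurrent, so it acts on a culture pair. A patient whose line was positive with a negative peripheral culture at an earlier draw may still count as colonized. A patient positive at both sites is not lost to the trial but is counted under bacteremia, where the third-row illustration still favours the device at 9 v 5. A reader might infer that every patient with a seeded line disappears from the colonization outcome; the wording does not support that.

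A reader might also infer that a working device will push the colonization proportion up. The documents do not support that either. It requires the device to lower the peripheral-positive share enough relative to its cut in line positivity, and no rate in the article says that it would. The preclinical work described is on bacterial load in the lumen, which would act first on line positivity.

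The planned correlations with line cultures, and Somers' d for the number of positive cultures, touch on the issue. Neither states an organism match or an event, and Table 3 lists no such outcome. Detailed matching rules may sit in a fuller document, but the two definitions are fixed here, and stated twice.

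Finally, the stakes are limited. The pilot's question is feasibility, these outcomes have no threshold, and the article itself doubts its power for them.

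**Conclusion.** The point holds in a limited form. As defined, colonization leaves out culture pairs positive at both sites, bacteremia has no line criterion, and no listed outcome is line-concordant bacteremia. The colonization proportion understates a device benefit whenever the peripheral-positive share of positive lines is lower on the device, and reverses it when cT/cC > (1−sC)/(1−sT). Across the assumed rates the result runs from no distortion (equal s) to 5 v 7 when line positivity is 10 v 8. All of these rates are assumptions.

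It would be tempting to conclude that a same-organism rule would yield a line-related bacteremia outcome. It would not: concordance does not prove that the line was the source, because the line sample is itself circulating blood.

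The primary feasibility outcomes are unaffected. This is an inexpensive improvement to the secondary efficacy data, not a defect that threatens the pilot.

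**What to change.** In Outcomes and Table 3, make the main colonization figure the proportion of patients per arm with any positive CVC-drawn culture. That culture is scheduled in all participants every 48 h and does not depend on what the treating team orders. Split these patients into:

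- (a) concurrent peripheral culture negative, which is the current definition;
- (b) peripheral culture positive with the same organism, labelled concordant bacteremia and not described as proven line-related;
- (c) peripheral culture positive with a different organism;
- (d) no concurrent peripheral culture taken.

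Report bacteremia with a negative line culture separately. State how a patient with several positive CVC cultures is placed in the split.

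The cost is wording and one extra table. Interventions already has the cultures analysed for organisms, and Outcomes already collects the peripheral results, so no new sampling is needed. The downside is that the any-positive figure and category (b) will include some events from other sources, so both should be read alongside category (a). Category (d) may be large, since peripheral cultures are taken only when the treating team orders them; showing it makes that visible.
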